**Methods:**

CRADLE-5 is a stepped-wedge cluster-randomised controlled trial of the CRADLE intervention compared to routine maternity care across eight rural districts in Sierra Leone (Bonthe, Falaba, Karene, Kailahun, Koinadugu, Kono, Moyamba, Tonkolili). Each district will cross from control to intervention at six-weekly intervals over the course of 1 year (May 2022 to June 2023). All women identified as pregnant or within six-weeks postpartum presenting for maternity care in the district are included. Primary outcome data (composite rate of maternal death, stillbirth, eclampsia and emergency hysterectomy) will be collected. A mixed-methods process and scale-up evaluation (informed by Medical Research Council guidance for complex interventions and the World Health Organization ExpandNet tools) will explore implementation outcomes of fidelity, adoption, adaptation and scale-up outcomes of reach, maintenance, sustainability and integration. Mechanisms of change and contextual factors (barriers and facilitators) will be assessed. A concurrent cost-effectiveness analysis will be undertaken.

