### Definitive stepped-wedge cluster-randomised controlled trial: May 2022 to June 2023

The CRADLE-5 trial is a pragmatic, mixed-methods, multi-district, stepped-wedge cluster-randomised controlled trial of the scale-up of the CRADLE intervention (CRADLE VSA device and CRADLE training package) into routine maternity care settings in SL and will be reported in line with the CONSORT stepped wedge cluster randomised trials update [18]. It will be accompanied by a concurrent process and scale-up evaluation between January 2022 to June 2023.

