## Interventions

### Explanation for the choice of comparators {6b}

Prior to transitioning to the CRADLE intervention, all women will be managed according to local guidelines (see https://mohs2017.files.wordpress.com/2018/04/sl-emonc-protocols-and-guidelines-a4-final.pdf to access national guidelines for emergency obstetric and newborn care). None of the districts will receive the intervention at time point 0. One district will be randomly allocated to receive the intervention at time point 1, whilst all the remaining areas contribute to the control at this time point. A second district is randomly allocated to the intervention at time point 2 and so on. Each randomisation cluster will cross over from the control to the CRADLE intervention at six-weekly intervals (see Fig. 2).

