### Sample size estimation {14}

Sample size estimation has been provided by the CRADLE senior statistician, using Stata version 13.1 and the methods of Hemming and Girling [28]. The power of the study will depend on three factors: (1) the design (eight groups, six-weekly time periods, around 1000 deliveries/period/centre), (2) the event rate and treatment effect (5% falling to 4%) and (3) the data structure, specifically the intraclass correlation coefficient (ICC) and cluster autocorrelation (CAC) coefficients.

Sample size calculations for longitudinal cluster randomised trials, such as our proposed stepped-wedge trials, necessitate the estimation of the correlation structure underlying the study. This entails assessing both the within-period intra-cluster correlations, which differ from conventional intra-cluster correlations due to their reliance on the period, and the cluster autocorrelation coefficients to account for correlation decay. For the purposes of the power calculation, we assume that there are up to 1000 deliveries per district per six weeks (half the 2000 we consider likely), across eight districts, each observed for 12 months. It is difficult to estimate more accurately at present, as we have no suitable multi-centre, multi-time period data in a single low-income country. However, if the ICC is suitably low and the CAC is suitable high, at the time of analysis, we do not predict any difficulties. We will obtain this information from our observational pilot data gathered in January to May 2022 in all eight districts of the study. Feasibility data suggests the CAC is likely to be 1. Therefore, even with an extremely high intra-cluster correlation of 0.5, power would be close to 100%. We have used https://clusterrcts.shinyapps.io/rshinyapp/ for the calculations. As per Fig. 3, with a CAC of 1, power will be more than adequate with 1000 women per month per centre.

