### Implementation {16c}

A new district will come on board every 6 weeks, at which point all facilities will have received their devices, and all frontline healthcare workers will have been trained in the CRADLE intervention model, as described above. This is a pragmatic trial and any deviation from the implementation plan will be recorded.

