
## Trial status

The current CRADLE-5 protocol is version 1.0 (December 2022). The trial received ethical approval from the Office of the Sierra Leone Ethics and Scientific Review Committee on 24th January 2022 and from the King’s College London, UK Research Ethic Committee on 27 January 2022. The trial opened on the 23 May 2022; all outcomes occurring from 23 May 2022 to 1 January 2024 will be included in the analysis.

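### The analysis window runs to 1 January 2024, but the design, six-week steps and power calculation describe one year ending June 2023

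*Protocol article*

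**What the plan says.** Four places in the protocol article fix a trial of about one year:

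- Abstract, Methods: "Each district will cross from control to intervention at six-weekly intervals over the course of 1 year (May 2022 to June 2023").
- Trial design, section heading: "Definitive stepped-wedge cluster-randomised controlled trial: May 2022 to June 2023". The same section describes a "concurrent process and scale-up evaluation between January 2022 to June 2023".
- Sample size estimation {14}: the calculation is "across eight districts, each observed for 12 months".
- Comparators {6b} and Implementation {16c} give the schedule. "None of the districts will receive the intervention at time point 0", and thereafter "A new district will come on board every 6 weeks".

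Trial status then says "all outcomes occurring from 23 May 2022 to 1 January 2024 will be included in the analysis".

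Three other provisions bear on the point. Outcomes {12} counts events up to 42 days after delivery and uses the deliveries in each six-week period and district as denominator. Data collection {18a} assigns a woman with an event to the period in which she first presented. Statistical methods {20a} describes the primary regression as linear trends with one step at introduction, and later in the same section names a multilevel logistic model with categorical time effects for primary and secondary outcomes.

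**The concern.** The two end dates define different primary datasets. The article mentions no extension, delayed roll-out or post-roll-out phase, and does not say how data from such a phase would enter the model.

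In a stepped wedge the randomised information comes from periods in which some districts are treated and others are not. Once every district has crossed, a strictly within-period comparison gains nothing from further periods. A regression with linear trends and a step does use them: they help fix each district's slope, and through the slope the size of the step. Seasonal or other non-linear change after roll-out can then move the estimated effect. Whether that matters here turns on the end date and on which time terms the primary model carries.

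**Working it through.** **1. The plan's own power figure.** Inputs from Sample size estimation {14}: eight districts, 1000 deliveries per district-period, 5% falling to 4%, CAC 1, ICC 0.5. The check used the generalised least squares variance for a stepped wedge with categorical periods, total variance p(1−p) at p = 0.045, two-sided 5%. With nine periods and eight steps, power is 99.9%, so the claim of nearly 100% reproduces. At ICC 0.01 power is 96.1% with nine periods and 98.8% with 14. The problem is not lost power.

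**2. Dates.** Inputs: opening on 23 May 2022, six-week (42-day) steps, one untreated baseline period, eight districts.

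- Last crossing with eight single steps: 8 × 42 = 336 days, giving 24 April 2023.
- Last crossing if the two districts paired before randomisation (Sequence generation {16a}) cross together: 7 × 42 = 294 days, giving 13 March 2023.
- End of nine periods: 9 × 42 = 378 days, giving 5 June 2023. This agrees with the June 2023 end date.
- Analysis window: 23 May 2022 to 1 January 2024 is 588 days; 588/7 = 84 weeks; 588/42 = 14 periods.
- Excess: (588 − 378)/7 = 30 weeks, or five periods. Ending anywhere from 1 to 30 June 2023 gives 30.6 to 26.4 weeks.

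**3. Balance (eight single steps).** Control district-periods are 8 + 7 + … + 1 = 36 in either window. Intervention district-periods are 72 − 36 = 36 with nine periods and 112 − 36 = 76 with 14. The control share falls from 50% to 32%.

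**4. Sensitivity of the estimate.** Assumptions: linear (absolute) scale, equal district-period sizes, region in the model description read as district, and a seasonal pattern common to all districts. The article gives no seasonal amplitude, so it is varied.

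The model is y = aₖ + bₖt + θX + error for district k and period t. The least-squares estimate of θ is a weighted sum of district-period rates. A seasonal term s(t) = A·sin(2π(t + φ)/8.70), where 365.25/42 = 8.70 periods per year, therefore adds Σw·s(t) to it. Its maximum over φ is A·√(C² + S²), where C and S are the weighted sums of the cosine and sine.

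| Model and crossing pattern | 9 periods | 14 periods |
|---|---|---|
| District trends + step, eight single steps, A = ±0.5 points | 0 | 0.354 |
| Same, A = ±0.25 points | 0 | 0.177 |
| Same, pair crossing together (seven possible positions), A = ±0.5 | 0.05 to 0.23 | 0.38 to 0.50 |
| District + categorical period effects, either pattern | 0 | 0 |

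Entries are worst-phase bias in percentage points; the target effect is 1.0 point. An amplitude of ±0.5 is 1.0 point peak to trough. With nine periods and single steps the weights sum to zero within every period, so a common pattern cancels. With 14 they do not.

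**5. Precision.** With district and categorical period effects, the standard error is 0.271 points for nine periods and 0.239 for 14.

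**The case against.** The later date might be explained by outcome follow-up. Events count up to 42 days after delivery and are assigned by first presentation, so some outcomes after June 2023 would belong to women who presented earlier. This stands in part. The 42 days account for about six of the 30 weeks, and antenatal presentation could add more. But Trial status takes all outcomes occurring up to the later date without limiting them to women who presented by June 2023, and the delivery denominator is counted period by period.

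A reader might infer that five treated-only periods were definitely added. The article does not show that. The later date could be an error, an extension or a late roll-out; the schedule figure is not available here, and Implementation {16c} expects deviations from the plan to be recorded. With a slipped roll-out, some of the added weeks could contain controls. The conflict would then lie with the six-week step and the 12 months per district.

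A reader might also infer that the trial's estimate is biased by a third of the target effect. That needs the linear-trend model, an assumed amplitude and the worst phase. The multilevel model with categorical time, named in the same section, removes a common seasonal pattern in either window. If the pair crosses together, the linear-trend model is not free of bias even with nine periods, so part of the weakness lies in that model and not in the end date. The permutation P-value should also remain valid, because relabelling districts carries the same calendar pattern; it does not repair the estimated risk ratio.

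Nor is 5 June 2023 the end of the randomised contrast. On the stated schedule the ninth period, from 24 April, already has no control district. It is the end of the planned design.

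**Conclusion.** The contradiction holds and leaves the primary dataset undefined: 14 six-week periods in Trial status against nine in the design. On the stated schedule, the 30 weeks after 5 June 2023 contain no control district. That conclusion rests on the six-week steps having been kept.

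The effect on the estimate is conditional. Under linear trends plus a step with eight single steps, the worst case is about 0.35 points for ±0.5 points of seasonality and half that for ±0.25, against none with nine periods. With the pair crossing together and ±0.5 points, it is about 0.4 to 0.5 against 0.05 to 0.2. With categorical period effects it is zero. The need for a single stated window does not depend on any of these figures.

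**What to change.** Reconcile the dates and state one primary analysis window. Define it by date of first presentation, as Data collection {18a} already does for events, and end it with the nine planned periods (5 June 2023 on six-week steps from 23 May 2022). Let 42-day outcome follow-up run to completion beyond that date; a hard stop on outcomes would truncate it. Report data from later presentations separately, under the maintenance and sustainability outcomes.

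If later periods are kept in the primary model, specify categorical period effects in place of linear trends alone. If the steps were in fact lengthened, correct the period length, the schedule and the 12-month figure throughout.

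The change is to wording, and the later data remain in use. The cost is a small loss of model-based precision: a standard error of 0.271 instead of 0.239 points with district and period effects. The article appeared on 15 September 2023, before the later cut-off, so the window could still be fixed at that time.

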## Data Availability

The datasets used and/or analysed during the current study will be made available from the corresponding author upon reasonable request.

## Abbreviations

SL: Sierra Leone
MMR: Maternal mortality ratio
BP: Blood pressure
CRADLE: Community blood pressure monitoring in Rural Africa: Detection of underLying pre-Eclampsia
VSA: Vital Signs Alert
MoHS: Ministry of Health and Sanitation
PHU: Peripheral health unit
WHO: World Health Organization
KCL: King’s College London
